### Recording Total Number of Steps Taken and Distance Covered per Training Session

For both groups, we recorded the total number of steps taken per session using a step watch (Orthocare Innovations), strapped around the participant’s nonaffected ankle. We also recorded the total distance covered per training session using a Stanley distance wheel. We positioned and secured the wheel at the front of the treadmill belt and measured the distance of the moving belt while the participant walked during their training session.

### Session Duration, Approach, and Progressions

Although participants in both groups had to complete 30 min of training, each single session lasted for a total of 90 min. This included the time for baseline and post measurements/calculations (ie, blood pressure and HR), setting up the HR monitor, determination of BWS level for training, and intervention trials with/without rest breaks. Although we encouraged participants to continuously train for 30 min, we recognized that participants might not have the necessary cardiovascular endurance to continually train for 30 min. Hence, we divided each training session into six 5-min bouts. We gave participants the option to take a seated or standing rest break after completion of each 5-min bout or combine multiple bouts (ie, 10 or more continuous minutes) followed by a rest. Thus, participants could individualize their training sessions, according to their comfort and ability. We encouraged all participants, regardless of their starting point, to aggregate more bouts as they progressed with training. Research assistants, conducting the training session, verbally encouraged participants while training to maintain their CWS and finish each training bout. However, they did not provide any manual assistance or external support during training.

### Criteria for Successful Training Session Completion

Although we encouraged all participants to complete their target 30 min of training per session, we used a threshold mark of 20 min to deem a session as “complete” and include it as a data point. If a participant did not achieve the minimum of 20 min, they had to repeat the session. At the completion of each session, we documented the above-described variables and entered them into a database. The PI and program coordinator monitored this database to ensure adequate study progress and safety of all participants.

### Total Time Taken for Each Training Session Visit

Participants on an average spent 1 to 1.5 hours per training session. This included the time for evaluation and measurement of baseline parameters (blood pressure and HR), choosing appropriate BWS level, training for 30 min (including rest breaks), and final posttraining blood pressure, HR measurement, restroom breaks, and drop-off and pick-up wait. We, thus, instructed participants to keep aside 2 hours on the days they were training and up to 3 hours on the days they were assessed.

### Participant Compensation

Participants were compensated US $10 per hour for the days that they trained and were assessed.

### Participant Adherence and Missed Session Makeover

Our goal was to provide adequate rest by alternating training days with rest days per week. To support participant adherence, the program coordinator worked with participants to pick alternate training days (3 times a week) and time slots during those days that suited the participant’s schedule. However, if a participant was not able to attend their session, we rescheduled it for 1 of the 2 free days of their training week. We requested participants to keep at least 2 hours aside for training on the days that they committed to come, and up to 3 hours aside for the days they would be assessed. We instructed participants that it was critical that they did not miss any training sessions and enrolled participants only after they had finished any travel obligations that would have interfered with their training. In addition, the program coordinator would also call and remind participants, a day before their training session, to come for training. If participants did not have a personal means of transport to come to the LocoLab for training, we arranged for alternate local public transport options, for example, local government run bus/van service. We also limited participants from rescheduling and extend their training sessions to a maximum of 7 consecutive weeks, to complete their 18 sessions, taking into account any rescheduled sessions because of personal commitments and/or national holidays. Participants were allowed a total of 5 rescheduled sessions.

### Minimizing Variability in Application of Procedures

We ensured that a minimum of 2 research staff members, one being a physical therapist, trained every participant during each training session. In total, we had 10 different research staff members, including 3 physical therapists, who regularly rotated and conducted all the training sessions to minimize expectation bias. The PI oversaw all training sessions and ensured strict adherence to all training protocols for both groups. The program coordinator and PI reviewed the progress of both training groups weekly and checked if all data were correctly documented. We ensured that no cointervention contamination occurred, by asking participants to refrain from attending any active lower limb physical therapy programs or participating in any walking intervention studies outside of our study.

### Reporting of Adverse Events

We defined an adverse event as an event that occurred during or after the training session when the participant was at the training site and trained staff members to report any adverse event pertaining to:

Fall to the ground (defined as an unintentional loss of balance)Any symptoms of angina or myocardial infarctionAny musculoskeletal injury during/after session trainingNew stroke or transient ischemic attackHospitalization for any causeDeath due to any cause.

Participants were also encouraged to report any symptoms (pain, soreness, numbness, etc) or signs of injury (inflammation, blisters, etc) that they experienced following training on returning home.

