### Robotic Treadmill Interface for Hands-Free Gait Training in Both Groups

Both groups trained on a novel robotic treadmill interface, which consists of a robotic-assistive device, called the KineAssist (KA; HDT Robotics, Salon Ohio, US) [28,29], synced to a Bertec treadmill [30]. The KA has been used in various studies to investigate both poststroke and nonimpaired walking biomechanics under different conditions [28,30-33]. The KA interacts with an individual walking inside it through a pelvic harness that secures their hips and waist through flexible cloth straps (Figure 2). The pelvic harness is attached to the KA’s pelvic mechanism that rests at the height of the individual’s center of mass (COM) and can provide vertical BWS (for a maximum body weight of 350 pounds and maximum height of 6 feet 5 inches). Two bidirectional force transducers at each hip enable the mechanism to sense drops in height and essentially *catch* the individual in the event of a misstep or loss of balance. This feature provides a safe environment and prevents falls during training. In addition, the force transducers and treadmill belt are paired through software to form a “force-velocity relationship”; the transducers sense the net force applied to the pelvic mechanism and send a signal to move the treadmill belt, making it an intent-driven treadmill. Thus, an individual walking inside the interface can control the speed of the treadmill and walk at their self-selected CWS (ie, intent-driven), with or without varying levels of BWS.

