**Figure 2 figure2:**
[figure not shown]
Individual poststroke walking in the KineAssist (KA) treadmill interface. The KA interface consists of a pelvic mechanism with 2 bidirectional force transducers and 2 interactive force rings attached to a pelvic harness and synced to Bertec treadmill.

Unlike nonrobotic environments that use motorized treadmills combined with overhead BWS harness systems, with or without handrails/external support [17,34,35], the KA interface eliminates reliance on any external support and offers the user control over their own gait speed through the intent-driven treadmill. When the *safety-catch* feature is triggered, force rings on either arm of the pelvic mechanism (see Figure 2) allow the researcher/therapist to interactively assist the individual back to a standing position by amplifying applied forces to each ring in the vertical direction. Thus, participants learn to address their falls and stumbles inside the interface as “errors” that they can then learn to formulate strategies to prevent, as opposed to developing fears and avoiding walking behaviors that might trigger them. The pelvic mechanism also allows movement of the COM in all 3 planes through 6 degrees of freedom (DOF). Unlocking the DOFs enables the individual to explore their limits of stability, whereas locking the DOF provides external stability for those with poor balance. This feature is unique in comparison with other robotic devices, which offer limited mobility or mobility in only one plane [36]. A trunk harness also secures the individual’s trunk when they walk inside the device and prevents excessive forward lean. The KA requires a short participant setup time (5-10 min) with assistance of only 2 individuals, due to a simple computerized user interface and an easily customizable pelvic mechanism. In comparison, more sophisticated robotic treadmill gait trainer systems or nontreadmill-based robotic exoskeleton systems tend to have a long setup time and require more than 2 individuals to help set up a participant [37-39]. We have previously published details on walking biomechanics in the KA interface and its different modes in another paper [24]. However, for this study, we used 3 distinct modes of the KA treadmill interface with and without varying levels of BWS:

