#### Challenge With Hands-Free Body Weight Support Gait Training

This group served as our “experimental” group, in that participants additionally performed 9 different essential challenging (C) mobility skills, along with HF walking during their 6-week training period (Table 1). The purpose of practicing these 9 essential training challenges along with HF walking was to offer participants opportunities to navigate through common environmental hazards that they may encounter during community ambulation. This protocol was innovative, as it involved exposing stroke survivors to challenging tasks that required strong skills in anticipatory and reactive balance and functional mobility. The KA’s safety features allowed us to provide participants with this experience and to treat losses of balance or stumbles as “learning experiences,” from which participants could learn to formulate new strategies without any negative consequences. At the start of each training week, the program coordinator would randomly select and assign 3 challenges for each session using a random number generator [27]. Participants practiced training for each of the 3 skills for 30 min (10 min per skill), without handrail support at 60% to 80% of their HR reserve intensity per session. We did not have a prescribed challenge progression for each skill; however, we encouraged participants to perform each skill at a level that was challenging for them (see task difficulty, Table 1).

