Hurdles	KA self-drive mode	To improve ability to step over objects in the environment (eg, curb)	Participants were instructed to walk at their CWS while stepping over a hurdle positioned at height to challenge foot clearance; 5 min practice per foot	If participants consistently cleared the current hurdle height, height increased by 1-inch increments
Perturations	KA self-drive mode	To improve reactionary balance control	Participants were instructed to walk at their CWS, while experiencing abrupt disturbances (ie, brief backward accelerations) to forward progression delivered by the KA software	If participants walked through forward perturbations without experiencing disturbances (ie, missteps or backward steps), the intensity of the perturbation would be increased
Backward walking	KA self-drive mode	To improve balance control, simulate instances where stepping backward to maneuver over obstacles	Participants walked backward	If the participant successfully walked backward, they were encouraged to step faster
Walking with foam shoes	KA self-drive mode	To improve ability proprioception, to walk on uneven surfaces, and stepping height	Participants walked with foam shoes strapped to their typical footwear. Shoes ranged from 2 to 6 inches in thickness	If the participant successfully maintained their CWS, the height of the foam shoes increased from 4 to 6 inches in thickness
Narrow stepping	KA self-drive mode	To decrease reliance on external support and improve dynamic balance	Participants walked on a straight infrared while taking narrow steps at their self-selected CWS without hand support or manual assistance	If the participant successfully maintained their CWS, they were verbally encouraged to walk faster

^a^KA: KineAssist.

^b^CWS: comfortable walking speed (m/s).

**Table 2 table2:** Summary of the hands-free and challenge with hands-free walking intervention training parameters.

Intervention	Hands-free walking	Challenge+hands-free walking
Duration	6 weeks	6 weeks
Total sessions	18 sessions	18 sessions
Weekly training	3 days a week	3 days a week
Session duration	1 hour	1 hour
Intervention duration	30 min	30 min
Training speed	Comfortable walk speed at chosen BWS^a^ level	Comfortable walk speed at chosen BWS level
Intervention goal	Perform 30 min of walking at fastest 10MWT^b^ with/without BWS as prescribed	Perform 30 min of walking at fastest 10MWT with/without BWS while performing additional walking skills

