Session design	5-min bouts × sets, or as long as continuously tolerated	5-min bouts × 6 sets, or 10-min bouts × 3 sets to allow for skill changes
Session goal	Target 60% to 80% of heart rate reserve during all trials	Target 60% to 80% of heart rate reserve during all trials
Locomotor challenge	Hands-free and without manual assistance	3 new randomized locomotor total challenges per day × 3 sessions=9 per week
Instruction	Maintain heart rate in the target zone while walking	Maintain heart rate in the target zone while performing different walking skills
Physiological measures monitored	Heart rate—using heart rate, monitor each minute; rate of perceived exertion—using Borg scale every 2 min; blood pressure—pre/post	Heart rate—using heart rate monitor each minute; rate of perceived exertion—using Borg scale every 2 min; blood pressure—pre/post
Additional session measurements	Total number of steps (using step watch) and distance covered (using distance wheel)	Total number of steps (using step watch) and distance covered (using distance wheel)
Rest breaks	Every 5 min if necessary; standing breaks if heart rate exceeded zone; voluntary breaks if requested by participant (rare)	Every 5 min if necessary; standing breaks if heart rate exceeded zone; voluntary breaks if requested by participant (rare)
Training personnel	Physical therapist × 1; research assistant × 1	Physical therapist × 1; research assistant × 1
Training setting	Clinical laboratory	Clinical laboratory

^a^BWS: body weight support.

^b^10MWT: 10-meter walk test.

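### The fall adverse event is named as reaching the ground but defined as any unintended loss of balance, so stumbles caught by the device would literally count as falls, probably more often in HF+C

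*Protocol article*

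**What the plan says.** The section Reporting of Adverse Events in the Protocol article gives staff a list of events to report. The first item reads "Fall to the ground (defined as an unintentional loss of balance"). The reporting window is "an event that occurred during or after the training session when the participant was at the training site", so it includes time on site outside the device.

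Four other places bear on how this item works:

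- **Device.** The section on the robotic treadmill interface says the pelvic mechanism senses a drop in height and catches the user at a misstep or loss of balance: "This feature provides a safe environment and prevents falls during training".
- **Use of the word fall.** The same section, in the text after Figure 2, says "participants learn to address their falls and stumbles inside the interface" as errors from which to develop strategies.
- **HF+C concept.** The section on challenge training describes "exposing stroke survivors to challenging tasks that required strong skills in anticipatory and reactive balance and functional mobility". It says the safety features allowed staff "to treat losses of balance or stumbles as" learning experiences.
- **HF+C tasks.** In the perturbation row of Table 1, participants walk "while experiencing abrupt disturbances (ie, brief backward accelerations) to forward progression delivered by the KA software". The perturbation is made stronger once the participant is no longer disturbed by it. The variable-speed row imposes abrupt changes of belt speed.

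No section separates a loss of balance caught by the device from a reportable fall.

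**The concern.** The label and the definition describe two different events, since a person can lose balance without reaching the ground. In many trials this would be loose wording with little effect. In this trial the device stops most losses of balance from becoming falls to the ground, and one arm practises tasks meant to disturb balance. The two readings can therefore give very different counts and a different contrast between the arms.

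What is at stake is how any fall count in the results papers can be interpreted. Under the definition, part of the HF+C count would be the training stimulus itself, recorded as harm. Under the label, the count would measure falls but would say nothing about caught losses of balance. A reader given only a number of falls could not tell which was meant. The primary outcome, comfortable walking speed, is not affected.

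**Working it through.** The article states no fall or stumble count, so there is no figure to reproduce. The check compares the two readings and then counts the exposure to which they apply.

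**Step 1. The two readings side by side**

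| Situation | Label: reaches the ground | Definition: unintended loss of balance |
|---|---|---|
| Stumble in the device, caught | Not reported | Reported |
| Fall to the ground in the device | Reported; near zero if the device works as described | Reported |
| Fall to the ground on site, outside the device | Reported | Reported |

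The readings differ in the first row only, and that is the row HF+C training is designed to fill.

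**Step 2. Exposure at full attendance**

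Inputs: 20 HF+C and 19 HF participants (Results); 18 sessions each over 6 weeks (Intervention Protocol, Table 2); three 10-minute skills per HF+C session (challenge training section); "3 new randomized locomotor total challenges per day × 3 sessions=9 per week" (Table 2).

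- HF+C sessions: 20 × 18 = 360.
- HF sessions: 19 × 18 = 342.
- HF+C skill blocks: 360 × 3 = 1,080.
- Perturbation blocks: nine challenges a week drawn from nine skills is about one block of each skill per week, so 6 per participant and 20 × 6 = 120 in HF+C. HF has none.

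**Step 3. Illustration of the gap between readings**

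The rate here is an assumption, because the article gives none. Take 0.1 to 1 caught loss of balance per perturbation block:

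- Definition: 120 × 0.1 = 12 up to 120 × 1 = 120 fall adverse events in HF+C from this one skill.
- Label: about 0 from the same blocks.
- Per HF+C participant: 12 / 20 = 0.6 up to 120 / 20 = 6 events.

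The other eight skills would add to the HF+C count.

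**Step 4. Direction of the contrast between arms**

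HF walking can also cause losses of balance, since those participants walk without handrails and explore their limits of stability. If ordinary walking produced the same rate r per session in both arms, the definition would give 360r against 342r, a ratio of 360 / 342 = 1.05. The arms would then be nearly equal. Any excess beyond that would have to come from the challenge tasks. Its direction is likely, given their purpose, but its size cannot be derived from the article.

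**The case against.** The strongest reply is that a sensible reading exists: the parenthesis may be meant to name the cause, a fall to the ground that follows an unintended loss of balance. The rest of the article leans that way, because it treats caught stumbles as lessons and not as harms. The article is also condensed, and detailed event forms may sit in the full protocol. This reply has some force as to intent. It does not remove the defect, because the printed text says the event is defined as the loss of balance. The article also uses the word falls for events inside the device while saying that the device prevents falls. This is a rule stated wrongly, not a detail left out.

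A reader might infer more than the document supports:

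- **That a safety endpoint or a planned safety comparison is invalid.** The article names neither. Adverse events appear in no outcome or analysis section.
- **That the label reading captures nothing.** Falls on site outside the device count under both readings.
- **That staff coded the item inconsistently.** Ten staff rotated, but at least two, one of them a physical therapist, ran each session. Staff were trained to report these events, the principal investigator oversaw all sessions, and documentation was reviewed weekly. None of this settles the definition, but nothing shows mixed coding.
- **That HF+C must show hundreds of falls.** Any such figure rests on an assumed rate.
- **That a true fall would be hidden among stumbles.** No text supports this.

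**Conclusion.** The point holds in a limited form. The adverse event item contradicts itself, and its literal definition would count intended, device-caught stumbles as fall adverse events, probably more in HF+C than in HF. The label would count only true falls, near zero in the device and possible elsewhere on site.

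The size of the difference is unknown. What the document fixes is the exposure: 360 HF+C sessions with about 120 perturbation blocks, against 342 HF sessions with none. This assumes full attendance and one perturbation block per HF+C participant per week. The range of 12 to 120 events is illustrative only.

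Confidence is high on the mismatch between label and definition, and moderate on the direction of the imbalance. The article does not show which reading staff applied. The item should be corrected before fall counts are reported, but it does not bear on the efficacy analysis.

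**What to change.** Reconcile the label and the definition. A fall adverse event should require unintentionally coming to the ground or a lower level, in or out of the device. A loss of balance caught by the device should be a separate class, reported as a training or feasibility observation and not as an adverse event.

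Data collection ended in January 2016, so a new per-session record of device catches cannot be added. For the results papers:

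1. State which definition staff applied during the trial.
2. Recode the existing fall reports into the two classes where the records allow.
3. Report both classes separately by arm, with the number of reports that could not be classified.

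The cost is a small amount of recoding. Some reports may lack the detail needed to classify them. If staff applied the label throughout, caught stumbles will not have been recorded as falls, and the second class may be incomplete or empty; the paper should then say so.
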